## Abstract

**Background:**

This article provides the rationale and methodology, of the first randomised controlled trial to our knowledge designed to assess the efficacy of progressive resistance training on cartilage morphology in women with knee osteoarthritis.

Development and progression of osteoarthritis is multifactorial, with obesity, quadriceps weakness, joint malalignment, and abnormal mechanical joint forces particularly relevant to this study. Progressive resistance training has been reported to improve pain and disability in osteoarthritic cohorts. However, the disease-modifying potential of progressive resistance training for the articular cartilage degeneration characteristic of osteoarthritis is unknown. Our aim was to investigate the effect of high intensity progressive resistance training on articular cartilage degeneration in women with knee osteoarthritis.

**Methods:**

Our cohort consisted of women over 40 years of age with primary knee osteoarthritis, according to the American College of Rheumatology clinical criteria. Primary outcome was blinded measurement of cartilage morphology via magnetic resonance imaging scan of the tibiofemoral joint. Secondary outcomes included walking endurance, balance, muscle strength, endurance, power, and velocity, body composition, pain, disability, depressive symptoms, and quality of life.

Participants were randomized into a supervised progressive resistance training or sham-exercise group. The progressive resistance training group trained muscles around the hip and knee at 80% of their peak strength and progressed 3% per session, 3 days per week for 6 months. The sham-exercise group completed all exercises except hip adduction, but without added resistance or progression. Outcomes were repeated at 3 and 6 months, except for the magnetic resonance imaging scan, which was only repeated at 6 months.

**Discussion:**

Our results will provide an evaluation of the disease-modifying potential of progressive resistance training for osteoarthritis.

**Trial Registration:**

ANZCTR Reference No. 12605000116628

## Background

### A rationale for implementing progressive resistance training as a disease-modifying treatment for knee osteoarthritis

Osteoarthritis (OA) is one of the most common musculoskeletal disorders in the world, affecting 9.6% of men and 18.0% of women ≥ 60 years of age worldwide [1]. In 1997, arthritis and other rheumatic conditions cost the United States (US) $86 billion dollars (equating to approximately 1% of the US gross domestic product) [2]. The development and progression of OA is multifactorial, with quadriceps weakness [3], joint malalignment [4], obesity [5], and abnormal mechanical joint forces [6] particularly relevant to this study.

### Is quadriceps weakness a cause or a consequence of knee OA?

Some studies conclude that quadriceps weakness is a possible preceding factor in the development of OA [7], while other studies support the possibility that quadriceps weakness contributes to disease progression [3]. Irrespective of the timing, once OA has developed, quadriceps weakness reduces the ability to decelerate leg movement and the leg is less able to absorb impulse loads transmitted through the tibiofemoral joint; leading to an acceleration of cartilage degeneration [3].

Medial compartment OA is associated with varus malalignment, and lateral compartment OA is associated with valgus malalignment [4]. A vicious cycle of malalignment then exists, whereby joint malalignment worsens the underlying excessive joint compartment forces (i.e. varus alignment increases the medial compartment load, and valgus alignment increases lateral compartment load in the knee during gait [8]) which contribute to OA progression in the respective compartments [4]. Knee malalignment is also considered to be a likely mediator of the OA-obesity relationship [8], as increased loading of malaligned, weakly supported joints accentuates the malalignment. Tendon stiffness is directly associated with muscle strength [9]; having stiffer tendons (less tendon elongation) improves the overall function and efficiency of the tendon as a stabilizer of the joint. By contrast, human studies have shown strengthening muscles (an adaptation to progressive resistance training (PRT)) increases stiffness and Young's Modulus in tendons around the knee joint which reduces the risk of tendon strain, and increases joint stability [9].

Muscle weakness may also play a role in the observed gender difference in the prevalence of OA, and the importance of obesity as a risk factor for OA. Firstly, radiographic OA is approximately twice as prevalent in women as it is in men [10]. Secondly, obesity is considered a risk factor for the development and progression of knee OA [8], and the association between obesity and OA is much stronger in women than in men [11]. The increased risk of knee OA associated with obesity appears to be related to mechanical rather than metabolic risk factors [8,12,13]. Women are weaker than men [14] and have lower muscle mass at all ages [15]. However, this gender disparity is diminished when lower extremity muscle strength is expressed per kilogram of muscle mass [16]. Reduced absolute and relative muscle mass in women means that they will be mechanically disadvantaged compared to men at the same absolute level of obesity or body mass index (BMI), as they have less muscle mass/strength to support the same body mass during standing and ambulation.

OA is considered a chronic degenerative disorder that is characterized by a loss of articular cartilage [17]. Due to the avascular nature of articular cartilage, cartilage development, maintenance and aging is dependent upon the type and magnitude of mechanical loading [18]. Immobilization or load deprivation alters the morphological, biochemical and biomechanical properties of articular cartilage [18], and ultimately results in decreases in cartilage thickness. More specifically, research has shown a significant 20% decrease in animal hyaline cartilage thickness of the femur following 11 weeks of immobilization [19]. By contrast, intermittent hydrostatic pressure during the early stages of OA in animals has been shown to maintain cartilage function [18]. In addition, animal studies have demonstrated a beneficial effect of moderate exercise on chondral lesion severity on induced (ACL-transected) OA [20], and strenuous wheel running exercise (6–12 km/day) is associated with normal cartilage (as opposed to fissuring, pitting, and fibrillation seen in the articular cartilage of sedentary hamsters who lived in individual housing without running wheels) [21]. This is supported by recent cross-sectional research revealing a higher tibial cartilage volume with both previous (baseline) and current (10 years after baseline assessment) participation in vigorous activity in healthy adults with no history of joint injury or trauma [22]. In addition, walking was also associated with a lower risk of bone marrow lesions [22]; which have previously been shown to be related to knee pain and cartilage degeneration [23,24].

### Specific rationale for resistance training exercise

Resistance training or strength training as it is commonly known, has beneficial effects on cardiovascular disease, insulin action, bone density, energy metabolism, psychological health and functional status in various elderly populations [25,26]. To date, approximately 18 randomized controlled trials implementing a resistance training intervention in isolation have been conducted in knee OA populations. Improving pain and disability in OA cohorts is a common hypothesis and primary outcome in many of these studies. However, changes in the underlying pathophysiology of the articular cartilage have not been reported in any of these trials. Based on the animal and human data reviewed above, progressive resistance training (PRT) also has the potential to reduce OA progression through 2 proposed pathways (see Figure 1). Increased muscle strength and tendon stiffness secondary to PRT [9] facilitates a strong balanced co-contraction of knee extensor and flexor muscles, and may thus improve joint stability and reduce varus and valgus instability [27-29]. In the first pathway by improving knee joint stability, abnormal loading and harmful forces generated during walking may be reduced; helping to protect and prevent further cartilage degeneration [3,30]. In the second pathway, the moderate controlled loading of PRT may stimulate cartilage synthesis [31], offsetting or delaying the changes usually seen in OA.

**Figure 1 F1:**
[figure not shown]
**Flow diagram detailing the rationale for implementing a progressive resistance training program for people with knee osteoarthritis**.

The purpose of this article is to provide a detailed rationale and methodology of the Resistive Exercise for Arthritic Cartilage Health (REACH) trial. By publishing the detailed methodology prior to the final outcome publication limits the potential for publication bias.

## Methods

### Study Design and Setting

This study was a double-blind randomized, sham-exercise controlled clinical trial. Ethical approval was obtained from The University of Sydney Human Research Ethics Committee on the 13^th ^December 2004 (Reference No. 12-2004/2/7848) and written informed consent was obtained from all participants. This study has been lodged with the Australian New Zealand Clinical Trials Registry (ANZCTR Reference No. 12605000116628). The study was conducted at the Cumberland Campus of University of Sydney in Lidcombe NSW Australia. MRI Scans were performed at the Symbion Clinical Research Imaging Centre in Randwick NSW Australia.

### Eligibility Criteria

Women over 40 years of age in stable health with primary OA in at least 1 knee, according to the American College of Rheumatology clinical criteria [32] were included. Participants were excluded if they had secondary OA (i.e. OA diagnosed due to trauma, surgery, or other disease process); joint injury, injection or surgery within the past 6 months or knee joint replacement; already participated in structured exercise more than 1 day per week during the previous 3 months; any contraindications to exercise and/or magnetic resonance imaging (MRI); severe functional limitation or cognitive impairment.

### Recruitment

Participants were recruited from April 2005 to December 2006 from cohorts of previous research studies conducted at the University, articles and advertisements in local newspapers, information talks at local community and senior citizen centres, flyers in local businesses, and word-of-mouth.

### Medical Screening

A telephone screening questionnaire was followed by a physician history and physical exam in potential subjects.

### Intervention

Participants randomized to the intervention group performed resistance training at 80% of their peak strength using pneumatic resistance machines (K400 model, Keiser Sports Health, Inc, Fresno, CA, USA). The exercises included unilateral knee extension, standing hip abduction and adduction; and bilateral knee flexion, leg press, and plantarflexion. All exercises were performed for 3 sets of 8 repetitions (6–9 sec/repetition) with 10–15 seconds rest between repetitions and 1–2 min rest between sets. Maximum strength tests (1 repetition maximum or 1RM) were performed fortnightly and a new 80% load was prescribed; in between strength tests participants were prescribed 3% increments in load per session as tolerated. An intensity rating of 15–18 on the Borg Rating of Perceived Exertion (RPE) scale [33] was considered optimal and was used to adjust the load between 1RM measurements to assure the intended continuous progressive overload. Exercises and or resistance were modified daily according to participants' symptoms. Full range of motion was utilized unless limited by pain. In some participants, severe pain throughout the range of motion required substitution of isometric exercises of particular exercises intermittently during the 6 month of training.

The sham intervention was designed to closely replicate virtually all of the elements of the active exercise condition (modality, setting, supervision, equipment, volume, duration, frequency) with the notable exception of intensity, as we hypothesized that intensity would be the critical prescriptive element leading to robust adaptations in both proximal (muscle and tendon strength/hypertrophy) and distal outcomes (cartilage morphology) outcomes.

Participants randomized to the sham-exercise group trained on the same equipment as the intervention group except hip adduction, and performed knee extension bilaterally. Minimal resistance was set on the machine (weight of bar/foot plates only) and no progression was introduced. Exercise volume was reduced to 2 sets of 8 repetitions, using same speed as in the PRT group.

Both groups trained 3 times per week for 6 months under supervision of an exercise physiologist at the University in a ratio of 1:1–3. If sessions were missed due to illness or holidays, those sessions were added onto the end of the 6 month intervention. Up to 1 month extension was allowed to complete the 78 sessions (compliance was calculated as the percentage attended out of 78 sessions available).

### Adverse events

A weekly questionnaire, administered in person or by phone was used to monitor adverse events plus changes in health status in all participants. A priori definition of any musculoskeletal or cardiovascular event attributable to testing or training (i.e. inflammatory response in knee joint, cartilage/ligament/muscle tear, fracture, fall, angina, etc.) were considered as adverse events [34].

Pain during a training session that was self-limited and not considered consistent with an injury (see above) was not considered an adverse event but may have resulted in an adjustment of training protocol to accommodate limitations. Protocol deviations or adjustments occurred for both the sham-exercise and the PRT group. The main deviation included changing from a dynamic to an isometric form of training (maximal intensity for PRT and sub-maximal intensity for sham-exercise group) if the dynamic mode was causing pain in the knee joint, reducing the intensity for the PRT group, and/or limiting the range of motion.

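### An event counts as adverse only if judged attributable to testing or training; that judgement is not stated to be blinded, so by-arm counts can be distorted in either direction

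*Protocol article*

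**What the plan says.** Under Adverse events, the protocol article sets an a priori definition: "any musculoskeletal or cardiovascular event attributable to testing or training". Its examples include joint inflammation, tissue tears, fractures, falls and angina. Pain in a session that was "self-limited and not considered consistent with an injury (see above) was not considered an adverse event", although it could lead to a change in training.

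The same section describes how safety information was gathered: "A weekly questionnaire, administered in person or by phone was used to monitor adverse events plus changes in health status in all participants". It also lists the main training deviations prompted by knee pain: isometric work in place of dynamic work, a smaller range of motion, and lower intensity in the PRT arm.

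Under Intervention, the PRT arm trains at 80% of peak strength, and "Maximum strength tests (1 repetition maximum or 1RM) were performed fortnightly and a new 80% load was prescribed". For sham, "Minimal resistance was set on the machine (weight of bar/foot plates only) and no progression was introduced". Both arms train "under supervision of an exercise physiologist at the University".

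The Blinding section covers MRI analysis, physical performance tests and self-report assessments, and states that follow-up performance testing was blinded for the participant only. Participants are blinded to which group the investigators prefer. Deciding whether an event is attributable is not mentioned.

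**The concern.** Attribution is normally a classification added after an event has been recorded. Here it decides whether the event exists as an adverse event at all. A fall or an episode of angina judged unrelated to testing or training is not one, and neither is any event outside the two named body systems.

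That judgement has an obvious cue. The same knee flare is easy to ascribe to training at 80% of peak strength and hard to ascribe to moving a bar or foot plate. Someone expecting PRT to help might lean the other way. Either tendency would move the by-arm counts without any change in what happened to participants.

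The pain exclusion adds a second judgement. Pain that changed the training, but settled and was not thought to be an injury, is absent from the count. It still bears on how well osteoarthritic knees tolerate high-intensity loading, which is a central safety question for this intervention.

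**Working it through.** The article gives no adverse event rate, safety margin or safety power, so there is no figure to reproduce. The check has two parts.

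**Reading the sections together**

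- *Is attribution a filter?* Yes. It is written into the definition (Adverse events).
- *Can the arm be seen?* Yes, by anyone present at training. Loads differ plainly between arms, and a physiologist supervises sessions (Intervention).
- *Is the attribution decision protected?* Not on the face of the text. Blinding does not list it. If the weekly questionnaire counts as one of the blinded self-report assessments, that protects collection of the information, not the decision on cause.
- *Is exposure to testing equal?* The fortnightly strength tests are described in the paragraph on the PRT arm only. Opportunities for an event to be put down to testing therefore appear unequal.
- *Was broader information collected?* Yes. The questionnaire covered changes in health status as well as adverse events, in all participants. Its items are not shown.

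**Illustration with assumed figures**

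Let p be the risk of any event in an arm and a the probability that an event is judged attributable. Then

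counted risk = p × a

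apparent risk ratio = (p_PRT / p_sham) × (a_PRT / a_sham)

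All values of p and a below are assumptions.

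| True risk, PRT vs sham | Attributed, PRT vs sham | Counted risk, PRT vs sham | True ratio | Apparent ratio |
|---|---|---|---|---|
| 20% vs 20% | 80% vs 40% | 0.20 × 0.80 = 16% vs 0.20 × 0.40 = 8% | 1.0 | 2.0 |
| 40% vs 40% | 80% vs 40% | 0.40 × 0.80 = 32% vs 0.40 × 0.40 = 16% | 1.0 | 2.0 |
| 20% vs 20% | 40% vs 80% | 0.20 × 0.40 = 8% vs 0.20 × 0.80 = 16% | 1.0 | 0.5 |
| 40% vs 20% | 40% vs 80% | 0.40 × 0.40 = 16% vs 0.20 × 0.80 = 16% | 2.0 | 1.0 |
| 20% vs 20% | 50% vs 50% | 0.20 × 0.50 = 10% vs 0.20 × 0.50 = 10% | 1.0 | 1.0 |

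The last row shows that equal attribution leaves the ratio intact; only a difference between arms distorts it. The fourth row shows a real doubling hidden.

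To put this on the trial's scale, take the target of 63 (Sample Size) and assume 1:1 allocation, so 63 / 2 = 31.5 per arm. With an assumed 30% risk in both arms, about 31.5 × 0.30 = 9.5 participants per arm would have an event. At 80% against 40% attribution, the counts would be 31.5 × 0.30 × 0.80 = 7.6 and 31.5 × 0.30 × 0.40 = 3.8.

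If reporting is equally complete in both arms, a count made without regard to attribution returns the true ratio in every row. Randomisation then does the attribution at group level: an excess of events in one arm is evidence of an effect without anyone judging single cases.

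**The case against.** The strongest reply is that a definition is not a reporting rule. The weekly questionnaire gathered health-status changes as well as adverse events in both arms, and nothing says the former will go unreported. The trial's objective is efficacy, adverse events are not among its listed outcomes, and the Statistical analysis section has no safety test. Joint harm is also measured in ways that need no attribution: blinded MRI of the most affected knee at baseline and 6 months, and WOMAC symptoms and disability in both arms. An article's silence on who judges attribution is ordinary condensation.

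Much of this stands, and it limits what may be inferred:

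- A reader might infer that attribution was made by unblinded staff and did differ by arm. The article names no judge and shows no difference. It only leaves the possibility open.
- A reader might infer that a planned safety comparison is biased. No formal comparison is described; the point applies to any by-arm count under the stated definition.
- A reader might infer that all pain leading to modified training is discarded. Only pain that is both self-limited and not considered an injury is excluded. Joint inflammation and tissue tears are named as adverse events, and pain-related changes are acknowledged as deviations in both arms.
- A reader might infer that an all-event count would be unbiased and free. Participants know what they lift, so self-report may itself differ by arm. The questionnaire's content is not shown, nor is it stated that reasons for modification were logged by session.

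The reply does not remove the rule. What is labelled an adverse event still depends on attribution, and a table of adverse events that follows the definition inherits that filter. MRI and WOMAC complement event counts but do not replace them: neither records falls, fractures or cardiovascular events.

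**Conclusion.** The concern holds in a limited form. The stated definition passes events through a causal judgement that the article does not say is blinded, in a trial whose arms differ visibly in load, so by-arm adverse event counts can be distorted upwards or downwards. The document does not show that they were.

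The size cannot be estimated from the article. Under the assumed figures, a two-fold difference in attribution doubles or halves the apparent risk ratio. This rests on the assumed risks and attribution probabilities, on 1:1 allocation for the participant counts, and on equally complete reporting in both arms. The efficacy results on cartilage are not affected.

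**What to change.** Make the main safety table all musculoskeletal, cardiovascular and other health events recorded on the weekly questionnaire, by arm and regardless of attribution. Give the number of participants with an event and events per unit of person-time. Show the attributed subset second, as a classification, and state who made it and whether that person knew the arm.

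Where training records allow, add by arm the number of participants or sessions with pain-related modifications: isometric substitution, reduced intensity or reduced range. If reasons were not recorded, say so.

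This changes tabulation only. It needs no new visits and alters no clinical rule; the article places the primary results in the future. The cost is low: one or two tables from information already gathered, plus some coding of health-status entries. The drawbacks are that the main table will include unrelated illness, and that self-report by participants who know their load remains a limitation to be stated beside it.

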### Objectives and Hypothesis

Our objective was to determine the efficacy of PRT as a disease-modifying intervention in women with OA.

We hypothesized that high intensity PRT would decelerate the tibial and femoral cartilage degeneration (i.e. reduce the rate of cartilage loss) in the knee affected most by OA and that high intensity PRT would lead to greater improvements in body composition, physical performance, symptoms and habitual physical activity level, compared to sham-exercise.

### Blinding

All participants were blinded to the investigators' hypothesis as to which was the preferred group. Analysis of the primary outcome (MRI scan of cartilage morphology) was double-blinded at all time points. All baseline and follow-up physical performance and self-report assessments were performed double-blinded; except for follow-up physical performance testing, which was single blinded (participant only). At the final assessment, participants were required to fill-out a Completion Questionnaire without the assessor present. This questionnaire assessed the participants' perception of whether they felt they had been in the "preferred group" to "modify cartilage, increase muscle mass and strength, reduce pain, and improve physical function".

